#### Group comparison analyses

2.8.2

*Primary group comparisons*: Between-group differences (insomnia vs. controls) will be assessed using appropriate statistical tests based on the data distribution and measurement level. Independent samples t-tests (or Mann-Whitney U tests for non-normal distributions) will be used to compare continuous variables. Chi-square tests will evaluate categorical variables.

*Secondary analyses*: Subgroup comparisons will examine differences based on sleep disorder risk (e.g., RLS symptoms, sleep apnea risk) and demographic factors. Analysis of covariance (ANCOVA) will control for potential confounders, including age, sex, and comorbid conditions.

*Multiple comparisons*: Given the large number of variables, false discovery rate (FDR) correction using the Benjamini-Hochberg procedure will be applied to control for multiple testing. Both uncorrected and FDR-corrected p-values will be reported to balance the discovery and rigor.

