### Participants

2.2

This study will recruit two parallel cohorts, an insomnia group and a normal sleeper control group. The inclusion and exclusion criteria for each cohort will be carefully defined to ensure a homogeneous sample and minimize confounding factors.

Participants in the insomnia group will be adults aged 19–70 years who report experiencing subjective insomnia symptoms, such as difficulty initiating sleep, difficulty maintaining sleep, or early morning awakenings, for at least three nights per week over the preceding three months. A score of 15 or higher on the Insomnia Severity Index (ISI) will be required to ensure that participants experience at least a moderate level of insomnia (21).

The normal sleeper control group will also consist of adults aged 19–70 years. To be included, these individuals must report experiencing insomnia symptoms less than three times per month, have an ISI score of less than 8, and report an average sleep duration of six hours or more per night over the preceding three months. Controls have no history of chronic insomnia or any major psychiatric illness and will also be required to comply with all the study procedures.

All participants in both groups are required to be willing to comply with all the study procedures, including the use of wearable devices and smartphone applications.

To minimize the influence of confounding factors, individuals meeting any of the following criteria were excluded from participation in either group: evidence of other primary sleep disorders such as untreated sleep apnea, narcolepsy, or other sleep-related breathing disorders; a current diagnosis of a major psychiatric disorder, including major depression, bipolar disorder, or schizophrenia, or a severe substance use disorder; the presence of cognitive impairment or a neurological disorder that could preclude valid self-report or compliance; participation in shift work or maintenance of an irregular sleep schedule within the past three months; and lack of access to a compatible smartphone or unwillingness to use the study’s smartphone application. The current use of hypnotic medications or supplements that have a significant effect on sleep was also an exclusion criterion.

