#### Statistical software and reproducibility

2.8.8

All analyses will be conducted using R (version 4.3.0 or later) and Python (version 3.8 or later) with specific packages documented for reproducibility. Version control using Git will track all analysis codes. Computational notebooks (R Markdown and Jupyter) will provide transparent documentation of analytical decisions and results.

Statistical significance will be set at α = 0.05 for primary analyses, with appropriate corrections for multiple testing. Confidence intervals (95%) will be reported along with p-values to provide the effect size context. Sample size considerations were based on effect sizes from published insomnia studies and power analyses of machine-learning applications.

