### Sample size and power considerations

2.9

Participant recruitment for this deep phenotyping study has been completed in accordance with the original protocol design. The study employed a rolling, observational recruitment framework, with the goal of achieving a sample size sufficient for robust multimodal analyses across clinical, behavioral, physiological, and digital domains. Based on feasibility and methodological considerations, the protocol specified minimum recruitment targets of approximately 330 participants in total, including at least 240 individuals with insomnia and at least 80 good-sleeper controls.

These targets were established to ensure statistical adequacy for the key analytic aims while maintaining the feasibility of comprehensive multimodal data collection. Power estimations at the design stage indicated that, under this allocation (unequal groups, α = 0.05), the study would achieve about 80% power to detect standardized mean differences of Cohen’s d ≈ 0.36, which represents a small-to-moderate and clinically meaningful effect commonly observed in sleep research. For correlational analyses involving continuous variables, a total sample of this magnitude provides approximately 80% power to detect correlations of r ≈ 0.15–0.16, assuming complete data pairs. For predictive analyses, a balanced-class equivalent sample of this scale would permit area under the curve (AUC) estimates around 0.70 with a standard error of approximately 0.03, corresponding to a 95% confidence interval of roughly ±0.06. These calculations reflect the expected precision and effect sizes typical of multimodal insomnia research rather than formal hypothesis testing for a single endpoint.

In practice, 338 participants were enrolled, comprising 249 individuals with insomnia and 89 good-sleeper controls, consistent with the predefined recruitment objectives. Within the insomnia group, severity distribution according to the Insomnia Severity Index (ISI) was mild = 130, moderate = 101, severe = 18. Analyses involving ISI will therefore treat severity as a continuous variable or use pooled strata where appropriate, given limited sample sizes in the extreme categories. The analytic plan includes standard measures to ensure that statistical modeling remains commensurate with the available data, including internal cross-validation and regularization to reduce overfitting in multivariate and machine-learning models.

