Several limitations may affect the interpretation and generalizability of the findings of this deep phenotyping protocol. This study has limitations related to its single-center setting and sample composition. While a single-site setting allows for rigorous standardization of data collection, instrumentation, and participant monitoring—crucial for integrating multimodal measures such as digital phenotyping, neuroimaging, and genomics—it inherently limits representativeness. Convenience sampling and hospital-based recruitment may introduce selection bias, potentially overrepresenting individuals with more severe insomnia symptoms. Future multicenter and cross-cultural studies including more heterogeneous clinical populations will be necessary to validate and extend the generalizability of these findings. This observational design precludes causal inferences regarding the relationships between the identified phenotypes and clinical outcomes. The 4-week monitoring period may not capture the long-term trajectories or seasonal variations relevant to comprehensive phenotyping. Consumer-grade wearable devices have inherent accuracy limitations compared with PSG, particularly in the classification of sleep stages. Despite these constraints, wearable-based monitoring offers important advantages in terms of ecological validity, enabling the assessment of habitual sleep patterns and minimizing the first-night effect commonly observed in laboratory sleep studies. To address this limitation, future studies would benefit from incorporating a validation sub-study directly comparing Fitbit-derived sleep measures with simultaneous PSG recordings.

The wearable data in this study were sampled at 5-minute intervals and derived from photoplethysmography rather than ECG, which limits the temporal resolution and accuracy of short term autonomic measurements. Nevertheless, this approach provides valuable insight into long term physiological patterns in real world settings, and future studies using research grade devices with raw PPG or ECG signals could further improve measurement precision.

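### The primary insomnia-versus-control tests for clinical and digital variables are unadjusted, and age and sex adjustment is ranked secondary in a non-randomised comparison

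*Protocol article*

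**What the plan says.** The protocol article's Data analysis plan (2.8) names three primary objectives, the first being the difference between the insomnia and control groups. Group comparison analyses (2.8.2) then ranks the tests. Under primary comparisons: "Independent samples t-tests (or Mann-Whitney U tests for non-normal distributions) will be used to compare continuous variables", and chi-square tests for categorical variables. No covariates are attached to any of these. Under secondary analyses: "Analysis of covariance (ANCOVA) will control for potential confounders, including age, sex, and comorbid conditions". The same section applies the Benjamini-Hochberg procedure and reports both corrected and uncorrected p-values. Statistical software and reproducibility (2.8.8) adds: "Statistical significance will be set at α = 0.05 for primary analyses".

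Participants (2.2) gives both cohorts the age range 19–70 and describes no matching or balancing on age or sex. It also sets one criterion for controls alone: "Controls have no history of chronic insomnia or any major psychiatric illness". The psychiatric exclusion that applies to both groups concerns a current diagnosis. On sampling, the limitations in the Discussion concede: "Convenience sampling and hospital-based recruitment may introduce selection bias".

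**The concern.** This is an observational comparison, so nothing in the design makes the two cohorts alike in age or sex. Many of the features to be compared, such as wearable sleep stages, heart rate, step counts and chronotype, plausibly depend on both. If the cohorts differ demographically, the crude contrast reflects insomnia and demographic composition together, and the plan would present that mixture as its primary result.

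The multiplicity correction does not help. Benjamini-Hochberg limits the share of chance findings among those declared. It does not shift a biased estimate back, and features that share a dependence on age would all be displaced by the same imbalance.

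The article itself names age and sex as potential confounders in 2.8.2. That sits poorly with leaving them out of the tests it calls primary. Recruitment is complete, so balance can no longer be achieved by design and analysis is the remaining lever.

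**Working it through.** **The plan's own figure.** Sample size and power considerations (2.9) states "the study would achieve about 80% power to detect standardized mean differences of Cohen’s d ≈ 0.36", for a target "including at least 240 individuals with insomnia and at least 80 good-sleeper controls". The sidedness of α = 0.05 is not stated; two-sided is used here.

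- SE = √(1/240 + 1/80) = 0.1291
- Power = Φ(0.36/0.1291 − 1.96) = Φ(0.83) = 79.6%

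The stated power is right. It refers to an unadjusted difference.

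**Achieved sample**, "comprising 249 individuals with insomnia and 89 good-sleeper controls":

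- SE = √(1/249 + 1/89) = 0.1235
- Detectable d at 80% power = (1.96 + 0.84) × 0.1235 = 0.346

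**Effect of imbalance on the unadjusted test.** Let g be the difference between cohorts in a covariate such as age, in SD units, and r the within-group correlation of that covariate with the feature. If there is no adjusted difference, the crude standardised difference is d = r × g. The rejection rate is Φ(d/SE − 1.96) + Φ(−d/SE − 1.96). The documents give neither r nor g, so every row with an imbalance rests on assumption.

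| r | g | spurious d | d/SE | rejection rate |
|---|---|---|---|---|
| any | 0 | 0 | 0 | 5.0% |
| 0.2 | 0.2 | 0.04 | 0.32 | 6.2% |
| 0.2 | 0.3 | 0.06 | 0.49 | 7.7% |
| 0.3 | 0.5 | 0.15 | 1.21 | 22.9% |
| 0.4 | 0.5 | 0.20 | 1.62 | 36.7% |

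These rates are for a single feature at the uncorrected 5% level. For scale, 0.15 is 0.15/0.36 = 42% of the effect the study was sized to detect.

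**Effect of adjusting.** In simulation at 249 versus 89 (8,000 runs per setting), with r = 0.3 and g = 0.5, the t-test rejected in 22.9% of runs and the covariate-adjusted test in 4.8%. Over all five settings simulated, the adjusted test stayed between 4.8% and 5.1%.

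The detectable difference after adjustment is (1.96 + 0.84) × √[(1 − r²)(1/89 + 1/249)/(1 − R²)], where R² is the share of group membership explained by the covariate. At r = 0.3 and g = 0.5, R² = 0.046 and the result is 0.338. For r from 0 to 0.5 and g from 0 to 0.8 it runs from 0.30 to 0.37, against 0.346 unadjusted. Power is essentially unchanged.

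**The case against.** The strongest reply is that adjustment is already planned. The next paragraph of 2.8.2 provides ANCOVA for age, sex and comorbidity, so a reader will see both results. This stands: the defect is the ranking, not an absence of adjustment.

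A reader might go further and infer that the crude test does not estimate a difference between the groups at all. The documents do not support that. A crude contrast is a valid description of how two cohorts differ, the article disclaims causal inference, and 2.9 presents its calculations as expected precision, not as a formal test of one endpoint. What the crude contrast cannot do is separate insomnia from demographic composition.

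A reader might also take it as established that the cohorts are unmatched and imbalanced. Matching is simply not mentioned, in an article that condenses a fuller protocol. The conceded selection bias concerns over-representation of more severe insomnia and says nothing about age or sex differences between the groups. With no imbalance the rejection rate is the nominal 5%.

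Scope is limited too. Specialized analyses (2.8.7) gives fNIRS comparisons general linear models and polygenic scores linear models with control for population stratification. Correlation and regression analyses (2.8.3) adds mixed models for daily digital data. The point therefore bears on the clinical and digital variables compared by two-sample tests. The rates above use the uncorrected cutoff; Benjamini-Hochberg cutoffs are usually stricter, although the plan reports uncorrected p-values as well.

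None of this is a reason to prefer the unadjusted test as the primary one.

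**Conclusion.** The point holds as a matter of ranking. For the clinical and digital variables under the first objective, the plan makes the comparison that is open to demographic confounding primary and the adjusted one secondary. It should be changed, but it does not invalidate the study, since the adjusted analysis is already foreseen.

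The size cannot be determined from the documents. The 8%, 23% and 37% figures illustrate assumed imbalances that give spurious differences of 0.06, 0.15 and 0.20. They rest on a single covariate acting linearly and on the uncorrected two-sided 5% level. They are not a forecast of the study's false-positive rate.

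The stricter psychiatric-history criterion for controls is a separate limitation. It would be tempting to treat age and sex adjustment as curing it, but that adjustment does not touch it. Adjustment for comorbidity could do so only in part, and psychiatric history is not among the baseline items listed in Clinical assessments (2.4).

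**What to change.** In 2.8.2, name the age- and sex-adjusted comparison as primary for the clinical and digital variables:

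- a linear model or ANCOVA for continuous features, with a rank-based or transformed version for skewed ones;
- logistic regression for categorical variables;
- Benjamini-Hochberg applied to the p-values from these adjusted models;
- the t, Mann-Whitney and chi-square tests reported as descriptive.

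Keep the ANCOVA that also adjusts for comorbidity as a secondary analysis. State the asymmetric psychiatric-history criterion as a limitation. If that history was recorded for the insomnia group, add a sensitivity analysis that leaves out participants with past major psychiatric illness; if it was not recorded, say so.

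The cost is small. Age and sex are collected at baseline (2.4), ANCOVA is already planned, about two degrees of freedom are lost, and no new data are needed.

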#### Correlation and regression analyses

2.8.3

*Bivariate associations*: Pearson correlations (or Spearman rank correlations for non-normal data) will be used to examine the relationships between subjective clinical measures (e.g., ISI scores) and objective digital phenotypes (e.g., sleep efficiency and circadian rhythm parameters). Correlation matrices will be visualized using heatmaps to identify patterns of association.

*Multivariate regression modeling*: Multiple linear and logistic regression models will be used to identify key predictors of sleep outcomes from the comprehensive digital phenotype set. Regularization techniques (LASSO, Ridge, and Elastic Net) will be employed to handle high-dimensional data and prevent overfitting. Model selection will utilize cross-validation procedures to optimize predictive performance while maintaining interpretability.

*Time-series analysis*: Longitudinal patterns in daily digital phenotypes will be analyzed using mixed-effects models to account for within-participant clustering. Time-varying covariates and random effects will capture individual trajectories and response heterogeneities.

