#### Sleep-related assessments

2.4.1

The sleep assessment battery was designed to capture multiple dimensions of sleep health and related behaviors that contribute to the pathophysiology of insomnia.

*Primary sleep measures*: The Insomnia Severity Index (ISI) (21, 22) serves as the primary outcome measure for insomnia severity, administered at screening for group allocation (≥15 for the insomnia group; <8 for controls) and weekly thereafter via the SOMDAY application. The Pittsburgh Sleep Quality Index (PSQI) (23, 24) assesses global sleep quality over the past month, whereas the Sleep Health Index (SHI) (25) provides a comprehensive measure of sleep health across multiple domains.

*Sleep disorder screening*: The Epworth Sleepiness Scale (ESS) (26, 27) measures daytime sleepiness, the Berlin Questionnaire (BQ) (28, 29) screens for obstructive sleep apnea risk, and the International Restless Legs Syndrome Rating Scale (IRLS) (30) assesses RLS (Restless Legs Syndrome) symptom severity.

*Sleep-related behaviors and cognitions*: Several instruments assess factors known to perpetuate insomnia. The Sleep Hygiene and Practices Scale (SHPS) (31, 32) evaluates sleep hygiene behaviors, whereas the Dysfunctional Beliefs and Attitudes about Sleep-16 (DBAS-16) (33) measures maladaptive sleep-related cognitions. The Morningness-Eveningness Questionnaire (MEQ) (34, 35) determines chronotype, Bedtime Procrastination Scale (BPS) (36) assesses bedtime delay behaviors, and Ford Insomnia Response to Stress Test (FIRST) (37) measures vulnerability to stress-induced sleep disturbance.

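### Correlations of Insomnia Severity Index with digital features are planned without regard to cohort, although cohorts are selected on that index, so a pooled r mixes case-control difference with severity gradient

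*Protocol article*

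**What the plan says.** Under Correlation and regression analyses (2.8.3), the article plans Pearson correlations, or Spearman for non-normal data, to examine "relationships between subjective clinical measures (e.g., ISI scores) and objective digital phenotypes", shown as heatmaps. No analysis set, stratification or cohort term is given.

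Under Sample size and power considerations (2.9), the target is "approximately 330 participants in total, including at least 240 individuals with insomnia and at least 80 good-sleeper controls". On correlations, the article says that "a total sample of this magnitude provides approximately 80% power to detect correlations of r ≈ 0.15–0.16", provided no pairs are missing; this refers to continuous measures in general. For group differences, "the study would achieve about 80% power to detect standardized mean differences of Cohen’s d ≈ 0.36". The enrolled sample is 249 with insomnia (130 mild, 101 moderate, 18 severe on the ISI) and 89 controls, 338 in total. ISI severity is to be treated as continuous or in pooled strata.

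Under Sleep-related assessments (2.4.1), the ISI is "administered at screening for group allocation", with a score of at least 15 for the insomnia group and below 8 for controls. The adjustment variables in 2.8.2 (age, sex, comorbid conditions) belong to the group-comparison ANCOVA and do not include cohort.

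**The concern.** When two groups are formed by their score on one variable and then pooled, any group difference in a second variable produces a correlation between the two, even if they are unrelated inside each group. Here that means a digital feature that merely differs between insomnia and control participants will also correlate with ISI.

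A reader of the heatmap could take such an r as evidence that the feature tracks how severe the insomnia is, when it may only repeat the group comparison of 2.8.2. Its size also depends on how many controls were recruited per case, which was a design choice, so it does not estimate the correlation in any defined population.

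**Working it through.** **1. The plan's own figure.** Fisher z with 80% power and α = 0.05 (2.8.8: "Statistical significance will be set at α = 0.05 for primary analyses"; two-sided assumed): detectable r = tanh[(1.960 + 0.842)/√(N − 3)].

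- N = 320: 0.156; N = 330: 0.154; N = 338: 0.152
- Insomnia cohort only, n = 240: 0.180; n = 249: 0.177
- Controls only, n = 80: 0.309; n = 89: 0.293

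The stated 0.15–0.16 is correct, and only for both cohorts together. Inside the insomnia cohort, power for r = 0.15–0.16 is 64–70% (n = 240) or 66–72% (n = 249).

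**2. Pooled r when the within-cohort association is zero.** Let p = 249/338 = 0.737, so p(1 − p) = 0.194. Then

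- pooled r = η × r_pb
- r_pb = d√[p(1 − p)] / √[1 + d²p(1 − p)]
- η² = the share of pooled ISI variance that lies between cohorts

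With d = 0.36 (section 2.9): r_pb = 0.36 × 0.4404 / √1.0251 = 0.157.

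**3. The ISI distribution.** The article gives no ISI means or SDs, so scores are assumed uniform over the integers in each band. A band of k integers has variance (k² − 1)/12. Controls (0–7) then have mean 3.5 and variance 5.25, and each seven-point band has variance 4.

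*As enrolled* (bands centred at 11, 18 and 25, with 130, 101 and 18 participants):
- insomnia mean = (130×11 + 101×18 + 18×25)/249 = 14.85; variance = 4 + 19.21 = 23.21
- within cohorts: 0.737×23.21 + 0.263×5.25 = 18.5
- between cohorts: 0.194×(14.85 − 3.5)² = 25.0
- η² = 25.0/43.5 = 0.57, η = 0.758

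*Under the written criteria* (ISI at least 15, with the 101:18 moderate-to-severe split kept as an assumption):
- insomnia mean 19.06, variance 10.29
- within cohorts: 8.96; between cohorts: 0.194×15.56² = 47.0
- η² = 47.0/55.9 = 0.84, η = 0.916

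**4. Result at 249/89.** Rejection rates are from 4,000 simulated studies per scenario, at unadjusted p < 0.05.

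| ISI distribution | d | pooled r | pooled test | partial r given cohort | insomnia cohort only |
|---|---|---|---|---|---|
| As enrolled | 0.36 | 0.12 | 59% | 5.1% | 5.3% |
| As enrolled | 0.50 | 0.16 | 86% | 5.0% | 5.0% |
| Written criteria | 0.36 | 0.14 | 75% | 5.2% | 5.1% |
| Written criteria | 0.50 | 0.20 | 96% | 5.2% | 5.4% |

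Fisher z agrees for the first row: atanh(0.1187)×√335 = 2.18, and Φ(2.18 − 1.96) = 0.59. At planned sizes (240/80) with d = 0.36, the pooled test rejects in 55% (as enrolled) and 72% (written criteria).

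**5. Dependence on the mix.** Keep the enrolled ISI distribution and d = 0.36, but recruit 1:1. Then η² = 0.25×128.9 / (0.25×128.9 + 14.23) = 0.69, η = 0.833, r_pb = 0.18/√1.0324 = 0.177, and pooled r = 0.15 instead of 0.12. Nothing about insomnia has changed, only the recruitment ratio.

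**The case against.** The strongest reply is that pooling is not stated. Section 2.8.3 names no analysis set, and the power sentence in 2.9 concerns continuous variables in general. The remark on treating ISI severity as continuous follows directly on the insomnia group's severity distribution, so it could mean analysis within that cohort. An article may leave such detail to an analysis plan. It stands that the pooled reading is an inference. It is a supported one: the wording is unrestricted, and the only detectable correlation given fits the total sample and not the insomnia cohort.

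Other parts of the reply stand and limit the point:

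- Section 2.8 lists group differences, subtypes and predictive models as the primary objectives. ISI–digital correlation is not among them, and 2.9 says its power figures are not for formal testing of a single endpoint.
- A significant pooled r is not a false positive. If the groups differ, the pooled correlation is truly non-zero; only its reading as a severity gradient is unsafe. The article does not say it will be read that way.
- The rejection rates are unadjusted, while 2.8.2 plans Benjamini–Hochberg correction. As enrolled with d = 0.36, rejection at p < 0.005 is Φ(2.18 − 2.81) = 27%. Whether a feature survives correction depends on the number of features and signals.
- Because ISI defines cohort, a cohort term can also remove genuine severity information, and an insomnia-only analysis narrows the ISI range. Neither is the only valid analysis.

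**Conclusion.** The point holds as a weakness in a supporting, exploratory analysis. As written, the plan allows an ISI–digital correlation that a group difference alone can produce. With no within-cohort association and d = 0.36, pooled r is about 0.12 as enrolled and about 0.14 under the written criteria, nominally significant in about 59% and 75% of studies. These figures assume ISI uniform within bands and use the screening bands; the article does not say which ISI occasion enters the correlations.

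A reader might infer more than the documents support:

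- *That the pooled r is only the group difference restated.* As enrolled, about 43% of ISI variance lies within cohorts, so r mixes the two sources.
- *That the power figure is wrong.* It reproduces; what it lacks is a counterpart for the insomnia cohort.
- *That the regressions share the flaw.* Section 2.8.3 does not define their outcomes or sample closely enough to say so.

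The 130 mild participants (ISI 8–14 by Table 1) contradict the entry score of at least 15, and sections 2.2, 2.4.1 and 2.9 must be reconciled. The point holds whichever way that is done.

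**What to change.** In 2.8.3, state that any claim of a severity gradient rests on correlations adjusted for cohort (partial correlations) or on correlations within the insomnia cohort, and that pooled correlations are reported alongside as descriptive.

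In 2.9, keep r ≈ 0.15–0.16 for total-sample or cohort-adjusted analyses and add r ≈ 0.18 for analyses within the insomnia cohort (n = 240–249).

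The cost is a few sentences and no new data. The partial correlation keeps nearly the full sample. The within-cohort analysis has a slightly less favourable detectable r and loses some ISI range.
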